### Study design

The ELEPHANT study, a mixed-method natural experiment, was designed to understand and evaluate the contribution of changes in trading hours for bars and clubs in Glasgow and Aberdeen to harms, services and costs in the local NTE and the implications for other major UK cities. Two different policy changes (described above) have led to later trading hours, which form the basis of the natural experiment. Hence, an interrupted time series (ITS) design will be used to compare the impact of alcohol policy changes between intervention and suitable control areas. ITS design is a widely used method for strengthening before-after study designs.^34^ A clear differentiation is required between preintervention and postintervention periods for an ITS study. The ‘time’ (date) of alcohol policy changes will be regarded as an interruption in the time series and will define preintervention and postintervention periods. Data will be collected before and after that interruption, and at least three variables, such as a time variable, a policy variable to indicate preintervention and postintervention periods and the outcome variable with values for each time point are required for an ITS study. A short-term outcome is also suggested for an ITS study. In our case, alcohol-related ambulance callouts and reported crimes are immediate effects of policy changes. The interruptions in Aberdeen occurred gradually following the approval date for the later trading hours of the 38 bars and clubs. ITS is one of the effective research designs to establish causality when RCTs are not practical.^51 52^ It permits statistical inference to be carried out to examine seasonality, autocorrelation, random fluctuations and heteroskedasticity, all of which might lead to bias in an assessment of the impacts of the interruption/intervention.^53 54^ In addition, we will use location-based control groups.^55^ Control groups which have not been exposed to the intervention under study have the potential to improve internal validity and will lead to a controlled ITS design.^56^ Further information on the process of control selection is described in the following section and is also published in the preprint statistical analysis plan.^57^ The economic evaluation frameworks employed alongside this design are outlined below.

### Overview of the economic analysis and logic model

Alongside the natural experiment design, we will conduct a CEA for the primary outcome of alcohol-related ambulance call-outs. This CEA will also revert to a cost analysis by monetising the alcohol-related ambulance call-outs. The policy of later trading hours for bars and clubs is considered a detrimental policy from a public health perspective, meaning the policy is expected to be associated with additional costs along with an expected increase in alcohol-related ambulance call-outs. The results of the CEA (and associated, monetised cost analysis) will be reported in terms of the incremental cost (additional cost required to implement the policy) associated with the incremental alcohol-related ambulance call-outs caused by the later trading hours, if any. In addition, a CCA will also be conducted in line with recent guidance, ‘*A Framework for conducting economic evaluations alongside natural experiments’*, to evaluate the economic impacts of later trading hours for bars and clubs in the NTE.^48^ Indeed, this is essentially a cost analysis, but for decision-making purposes, we will further deconstruct this into a CCA by reporting multisectoral costs and consequences. CCAs have been recommended for complex interventions that have multiple consequences and that are difficult to measure in a common unit. It includes all types of consequences, including health, non-health, negative and positive effects. It aims to give decision makers a comprehensive summary of the different costs and consequences, so a wider societal perspective will be taken to conduct the CCA to capture all possible costs and consequences that are feasible to measure. The CCA will be performed from the healthcare system, the criminal justice system and the wider societal perspective. Within the CCA framework, we will also consider retailer, social service and third sector perspectives by drawing evidence from the qualitative studies of the ELEPHANT study (see the interview topic guides for a qualitative study in online supplemental appendix 1). The CCA will assess the consequences of later trading hours for bars and clubs by measuring incremental alcohol-related ambulance call-outs and reported crimes in natural units. We will then identify, measure and value the associated resource costs across multiple sectors, including health sector, criminal justice system, business sector and third sector. The health sector will cover ambulance service costs, A&E service costs and inpatient care costs. The criminal justice system will account for police service costs, justice system costs and the costs of physical and emotional harm. The retail or business sector costs will include application processing costs, venue operating costs and staff salaries for the later trading hours. The third sector will include costs associated with the voluntary organisations such as street pastor, taxi marshal, etc. We will report the monetised values of incremental costs corresponding to these negative consequences across sectors. We cannot measure intangible costs/benefits (eg, consumer pleasure/losses) within the scope of our study. However, qualitative evidence on the retailer benefits (eg, additional profits/loss) and consumer benefits will be reflected in our discussion.

The economic evaluation will be conducted separately for the Aberdeen and Glasgow cities. An economic evaluation logic model has been developed (figure 1), building on the main study systems map. To conduct this complex economic evaluation, we have identified all possible resource uses and consequences, and our logic model (a conceptual framework) illustrates the causal pathways and interconnected linkages between these resources and consequences.^58^

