**Methods and analysis:**

The research design is an economic evaluation alongside a natural experiment within the ELEPHANT study carried out in Glasgow and Aberdeen. The economic evaluation has been designed to identify, measure and value prospective resource impacts and outcomes to assess the costs and consequences of local policy changes regarding late night trading hours for bars and clubs. A number of economic evaluation frameworks will be employed. A cost-effectiveness analysis (CEA) is appropriate for assessing the effectiveness of complex interventions when the impacts of policy are measured in natural units. Therefore, a CEA will be conducted for the primary consequence, alcohol-related ambulance call-outs, using a health service sector perspective. Since this outcome is essentially a cost, the CEA will also be reported as a cost-analysis. A cost-consequence analysis will also be performed for the primary and secondary consequences including all ambulance call-outs and reported crimes to evaluate the full economic impacts of later trading hours for bars and clubs in the night-time economy. The analysis will be conducted from a wider societal perspective, including health sector, criminal justice system, business and third sector perspectives and will be in line with the recent National Institute for Health and Care Excellence guidance and recommendations.

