### Resource use/costs

The cost components for this complex natural experiment involve integrating multiple NTE components, from differing perspectives, that could be affected by the policy changes in Aberdeen and Glasgow. There are multiple resource use components that we will endeavour to consider in costing. The costs related to the implementation of policy changes are considered from the retailer perspective. The retailer cost components will include administrative costs related to obtaining permission for later trading hours and the costs to manage and operate premises during these later hours, including staff salaries, venue maintenance and other associated costs. Due to a lack of data, we are unable to estimate costs for all venues from the retailer perspective. However, evidence from the qualitative studies (two qualitative studies were designed within the ELEPHANT study to understand the policy changes at system level and at venue level) and published sources will be used.

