#### Perspectives

The base-case analysis (CEA) will be conducted from an National Health Service (NHS) perspective.^58^ We will identify, measure and value the cost of ambulance services, emergency services and hospitalisation services to inform decision makers with a particular focus on the health sector (table 1). The later trading hours may not only impact health services, but may increase criminal justice system costs.^35 36^ Hence, in line with the array of health and non-health sectors consequences, the CCA will incorporate health services, the criminal justice system and societal perspectives. In addition, in the sensitivity analysis, retailers’ and third sector organisations’ perspectives will be incorporated into the societal perspective.

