### Economic data analysis

#### Analysis of costs and consequences

The economic evaluation will be conducted separately for Glasgow and Aberdeen. First, we will evaluate the impact of policy changes on harms, then we will conduct a CEA, cost analysis and CCA. Regression methods will be used to estimate effectiveness, that is, the impact of policy changes in Aberdeen and Glasgow. We will fit autoregressive integrated moving average (ARIMA) models with the weekly total counts for the primary and secondary consequences to assess the impact of policy changes (table 1). Such models account for autocorrelation and underlying temporal trends, and we will use Akaike information criterion and Bayesian information criterion to determine the best fitting ARIMA models. After a best fitting model is determined, we will then add the intervention variables to measure the effect size (impact of policy changes).

We will assess whether changes in the primary outcome (alcohol-related ambulance call-outs) have been caused by later trading hours. Where fewer or greater numbers of alcohol-related ambulance call-outs are found to have resulted from the policy changes, the unit cost of each resource will be multiplied by the absolute number of fewer or additional outcomes/consequences, for each city, before and after the policy changes.

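### The base-case cost-effectiveness analysis defines its incremental cost as a retailer cost that its NHS perspective excludes, and the NHS costs that remain are only a multiple of the call-outs themselves

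*Protocol article*

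**What the plan says.** Five statements in the protocol article bear on the base case.

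- **What the incremental cost is** (Overview of the economic analysis and logic model). Results of the CEA, and of the monetised cost analysis tied to it, are to be given as the "incremental cost (additional cost required to implement the policy) associated with the incremental alcohol-related ambulance call-outs caused by the later trading hours".
- **Who bears it** (Resource use/costs). "The costs related to the implementation of policy changes are considered from the retailer perspective". Table 1 lists two inputs under resource use, the cost of obtaining permission and the cost of operating the later hours.
- **Perspective of the base case** (Perspectives). "The base-case analysis (CEA) will be conducted from an National Health Service (NHS) perspective". Its content follows directly: "We will identify, measure and value the cost of ambulance services, emergency services and hospitalisation services". Retailers come in elsewhere: in sensitivity analysis, "retailers’ and third sector organisations’ perspectives will be incorporated into the societal perspective". The abstract agrees: "a CEA will be conducted for the primary consequence, alcohol-related ambulance call-outs, using a health service sector perspective".
- **How the health costs are computed** (Analysis of costs and consequences). Where the policy changed the number of call-outs, "the unit cost of each resource will be multiplied by the absolute number of fewer or additional outcomes/consequences". The Consequences section attaches ambulance, A&E and admission costs to the call-outs and names no NHS cost that arises independently of them.
- **What is conceded** (abstract, Methods and analysis). "Since this outcome is essentially a cost, the CEA will also be reported as a cost-analysis". The Objective and Overview sections repeat this conversion.

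**The concern.** The first three statements cannot all hold. If the incremental cost is the cost of implementing the policy and retailers bear it, an NHS-perspective analysis has nothing to put there. If the NHS perspective governs, the incremental cost must be the health-care cost of the call-outs, which is not what the Overview section defines.

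The second route has a further problem. Call-outs are the effect measure, and under the costing rule they are also the only driver of NHS cost. Setting that cost against the call-outs as a cost per call-out compares a quantity with a multiple of itself. The result would describe the price of a call-out and not the consequence of the policy.

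At stake is the result labelled as base case, in a study whose findings are meant to inform licensing boards. A stable cost per call-out could be taken for a cost-effectiveness finding when the policy effect has dropped out of it.

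**Working it through.** The article gives no unit cost, call-out count or cost-effectiveness result, so there is no figure to reproduce. The check is algebra with an illustration.

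**Inputs**

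- *D*: incremental call-outs, from the time-series models (Analysis of costs and consequences).
- *a*, *e*, *h*: unit costs of an ambulance response, an A&E attendance and an admission. Assumed: £300, £200, £2,000.
- *p*: share of call-outs conveyed to hospital. The article will collect conveyance (Consequences) but gives no value. Assumed: 0.7, range 0.5 to 0.9.
- *q*: share of conveyed call-outs admitted. The Uncertainty and sensitivity analysis section gives scenarios of 5%, 10% and 15%; zero is added here for the option of costing A&E only.
- *I*: implementation cost, borne by retailers. Assumed £100,000 for illustration.

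**Reading 1: the implementation-cost definition taken literally.** Cost per incremental call-out = *I*/*D*. From the NHS perspective *I* = 0, so the result is 0 for any non-zero *D*. If the retailer cost is counted:

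- *D* = 50: 100,000/50 = £2,000
- *D* = 200: 100,000/200 = £500
- *D* = 1,000: 100,000/1,000 = £100

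This varies with the effect, so it is not circular, but it is no longer an NHS-perspective result.

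**Reading 2: the NHS perspective with the stated costing rule.** With *p* and *q* fixed,

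NHS incremental cost = *D* × [*a* + *p*(*e* + *q h*)]

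and dividing by *D* leaves *a* + *p*(*e* + *q h*), which does not contain *D*. With *p* = 0.7 and *q* = 0.10 this is 300 + 0.7 × (200 + 0.10 × 2,000) = 300 + 280 = £580.

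| *D* | Incremental NHS cost | Cost per call-out |
|---|---|---|
| -200 | -£116,000 | £580 |
| -20 | -£11,600 | £580 |
| 20 | £11,600 | £580 |
| 200 | £116,000 | £580 |
| 1,000 | £580,000 | £580 |

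The middle column changes in size and sign with the policy effect; the last does not. Across *p* = 0.5 to 0.9 and *q* = 0 to 0.15 the last column lies between 300 + 0.5 × 200 = £400 and 300 + 0.9 × (200 + 300) = £750, and within each combination it is again the same for every *D*. At *D* = 0 it is undefined.

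**Reading 3: the conveyed share shifts with the policy.** Assume 5,000 baseline call-outs, *q* = 0.10 and *D* = 50, so 5,050 afterwards. Each conveyed call-out then costs 200 + 0.10 × 2,000 = £400 beyond the ambulance.

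- *p* stays at 0.70: £580, as before.
- *p* rises from 0.70 to 0.72: conveyed call-outs change by 0.72 × 5,050 − 0.70 × 5,000 = 136. Cost = 300 × 50 + 400 × 136 = £69,400, or £1,388 per call-out.
- *p* falls from 0.70 to 0.68: the change is 0.68 × 5,050 − 3,500 = −66. Cost = 15,000 − 26,400 = −£11,400, or −£228 per call-out.

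The cancellation therefore depends on a fixed conveyance share.

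**The case against.** Four arguments can be made for the plan as written.

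**No ratio is named.** The article never mentions an incremental cost-effectiveness ratio or a cost per call-out. Its sentence on reporting can be read as two quantities side by side. This stands, and the point about cancellation is therefore conditional on such a figure being reported. It does not remove the conflict over what the incremental cost contains, which exists on either reading. And if no ratio is meant, the CEA is the cost analysis under another name.

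**Any ratio need not equal the average unit cost.** A reader might infer that it always does, whatever the policy did. The documents do not support that: it is undefined at no effect, and Reading 3 shows that it moves if the conveyed share changes. However, the models are planned for the consequences in Table 1, conveyance is not among them, and the admission shares are scenario values. As written, no policy effect on either share is estimated.

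**The issue is disclosed and useful analyses are planned.** A reader might infer that the study cannot answer its question. That goes too far. The cost analysis, computed by the stated costing rule, varies with the effect, and the cost-consequence analysis shows effects in natural units with costs by sector. The disclosure does not settle the conflict, though: the CEA is still called the base case, and the sentence defining incremental cost as implementation cost covers the cost analysis too.

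**The definition itself is not circular.** This also stands. The implementation-cost wording shows a contradiction; circularity arises only when the NHS perspective and the costing rule are applied in its place.

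**Conclusion.** The base-case CEA is internally inconsistent. Its incremental cost is defined as something retailers pay, and its perspective leaves retailers out. This rests on the text alone and needs no assumption.

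What remains under the NHS perspective is a multiple of the incremental call-outs. If a cost per incremental call-out is reported, it carries no information on the size or direction of the policy effect, given a non-zero effect and fixed conveyance and admission shares. The pound values are illustrations on assumed unit costs; the cancellation does not depend on them.

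Following the plan thus gives either a cost outside the stated perspective or, if expressed per call-out, an uninformative base case. The cost analysis, once its incremental cost is defined correctly, and the cost-consequence analysis are not undermined.

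**What to change.** 1. Reconcile the Overview section with Resource use/costs and Perspectives: delete implementation cost from the definition of incremental cost under the NHS perspective, for both the CEA and the cost analysis.
2. Name the planned cost analysis as the base case: incremental NHS cost per city per year, shown beside the incremental call-outs, with the uncertainty of the effect estimate carried through to the cost. The last element may already be in the separate analysis plan, which is not shown here.
3. Report no NHS cost per call-out. If a ratio is kept, compute it outside the NHS perspective, leave the cost of the call-outs out of its numerator, and say who bears the cost. Such a numerator would rest on limited data, since the article says retailer costs cannot be estimated for all venues.

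The price is that the CEA label is dropped or demoted. The rest is wording in the protocol and final report; no new data are needed, and the cost analysis is already planned.

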**Outcomes/consequences**		
** *Negative consequences* **		
Alcohol-related ambulance call-outs (primary consequences)	Yes	Scottish Ambulance Service (time series data)
Total ambulance call-outs (secondary outcomes)	Yes	Scottish Ambulance Service (time series data)
Reported crimes (secondary outcomes)	Yes	Police Scotland (time series data)
Alcohol-related road traffic accident	No	Design not amenable to data capture.
Reduced workforce participation due to sickness	No	Design not amenable to data capture.
Reduced household labour due to sickness	No	Design not amenable to data capture.
Reduced workforce and household labour due to premature mortality	No	Design not amenable to data capture.
Increased burden to the social service sectors	Yes	Data from the qualitative studies and secondary published sources will be used.
Increased additional consumer’s spending during later or expanded premises hours	No	Design not amenable to data capture

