Social service sector (third sector) costs include expenses incurred by voluntary organisations engaged in the NTE, such as volunteer training, medical kits and paramedic services. Consumers’ additional costs during the expanded hours include costs on alcohol, food and other items. Findings from qualitative studies and secondary sources, such as the websites of voluntary organisations, will be used to identify, measure and value the costs to the social service sectors. However, due to a lack of available data, we will not be able to measure the additional costs to consumers during the later trading hours.

Different cost components from multiple sectors are also associated with the primary (alcohol-related ambulance call-outs) and secondary outcomes (all ambulance call-outs and reported crimes). Alcohol-related ambulance call-outs are associated with the costs of major alcohol-related healthcare services including alcohol-related hospital admission, alcohol-related emergency services and ambulance service cost. Costs associated with reported crimes relate to three main cost areas: costs in anticipation of crime, costs as a consequence of crime and costs in response to crime.^64^ The costs of ambulance services and alcohol-related healthcare services will be measured using existing national Information Services Division (ISD) Scottish Health Service cost data. The ISD data will provide the unit cost of each alcohol-related ambulance service, as well as the cost of any subsequent health service utilisation. We will collect ambulance call-out data and whether these call-outs conveyed to hospital or not. If conveyed to the hospital, this will incur costs for the A&E department along with the cost of ambulance services. If an ambulance call does not convey to hospital, this will incur only the cost of ambulance services. Further, we will explore existing evidence from the literature on the percentage of alcohol-related ambulance call-outs that necessitate hospitalisation. Otherwise, we will analyse the costs within the A&E department only due to lack of data to link ambulance call-outs with hospitalisation and will incorporate them into the scenarios analysis. The unit cost for the reported crimes will be adopted from published sources, for example, ‘the economic and social costs of crime’.^64^

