#### Time horizon

Deciding the time horizon for an economic evaluation is crucial and usually guided by the periods used to measure costs and consequences.^65^ Data for the primary (alcohol-related ambulance call-outs) and secondary consequences (all ambulance call-outs and reported crimes) will be collected from 2015 to 2022 to assess the impact of policy changes. The policy changes began in 2017 in Aberdeen and in 2019 in Glasgow. The most recently available cost data (unit costs) will be collected, expressed in pounds sterling (£), and if necessary, inflated for the different years using the Health Services index. All costs and consequences will be reported within an annual cycle, so there will be no need to apply discounting.

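### The criminal justice cost line includes victims' physical and emotional harm, and the only price index named for unit costs, crime costs included, is a health one

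*Protocol article*

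**What the plan says.** The section on the overview of the economic analysis and logic model assigns costs to sectors. For health: "The health sector will cover ambulance service costs, A&E service costs and inpatient care costs". For justice: "The criminal justice system will account for police service costs, justice system costs and the costs of physical and emotional harm". It goes on: "We will report the monetised values of incremental costs corresponding to these negative consequences across sectors". Shortly afterwards it states: "We cannot measure intangible costs/benefits (eg, consumer pleasure/losses) within the scope of our study". Criminal justice is listed there, and again under Perspectives, as a viewpoint of its own beside the health and societal ones.

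The Consequences section divides the cost of reported crime into three areas: "costs in anticipation of crime, costs as a consequence of crime and costs in response to crime". The section on uncertainty and sensitivity analysis gives examples of each: alarms and CCTV for anticipation, stolen or damaged property for consequence, and police and the justice system for response. Crime unit costs are to come from published sources. Neither their breakdown nor their price year is given.

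The Time horizon section says that the latest available unit costs will be collected and, where needed, "inflated for the different years using the Health Services index". No other index is named, and no class of cost is excepted.

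**The concern.** A sector perspective is useful because it tells that sector what it would bear. A line that combines agency spending with the monetised suffering of victims does not do this. A justice agency or a licensing board would read it as a burden on police and courts, and the article says that findings will be shared with licensing boards before publication. The line is misdescribed even if it is never added to anything else.

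The placement also sits uneasily with the sentence on intangibles. Emotional harm is intangible and is to be valued, while intangible benefits to consumers are left out.

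The index raises a different issue. Health-service prices need not move with the prices behind crime, retail or voluntary-sector costs. As written, one health index would carry all of them to the reporting year.

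**Working it through.** The article gives no sector cost, crime unit cost or index value, so there is no figure to reproduce. The check compares the sections and adds illustrations with stated assumptions.

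**1. Criminal justice line**

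- The Overview puts three items in the line: police (p), justice system (j), and physical and emotional harm (h), each per reported crime.
- The Uncertainty section gives police and justice as the example of response costs. It does not name physical and emotional harm in any area. Such harm is not an agency's response to crime, and it fits the consequence area best.
- With N incremental crimes, the reported line is N × (p + j + h) and the agency burden is N × (p + j). The relative excess is h / (p + j), which is above zero whenever h is.
- The section on analysis of costs and consequences allows for fewer as well as more events. If crimes fell, the same ratio would overstate the saving.
- The values of p, j and h are not in the article, so no percentage can be given.

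**2. Price index**

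Let g be the annual gap between the health index and a suitable index, and y the years between a unit cost's price year and the reporting year. The relative error is (1 + g)^y − 1. Both g and y are assumptions.

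| Gap per year | 3 years | 5 years | 8 years |
|---|---|---|---|
| 0.5 points | 1.5% | 2.5% | 4.1% |
| 1 point | 3.0% | 5.1% | 8.3% |
| 2 points | 6.1% | 10.4% | 17.2% |

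For example, 1.02^5 − 1 = 0.104. If y = 0, the error is zero. The direction depends on which index rises faster, which the article does not say.

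**3. Overlap between lines**

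- Table 1 lists "Total ambulance call-outs (secondary outcomes") beside the alcohol-related ones, which they contain. The change in all call-outs equals the alcohol-related change plus the non-alcohol change.
- If the non-alcohol change were zero and unit costs equal, adding both lines would give twice the alcohol-related cost. This requires the lines to be added, and no section plans that.
- An event that is both a call-out and a reported crime would have its health care counted twice only if a total were formed and the crime unit cost contained health care. The article establishes neither.

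**4. Base case**

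Under Perspectives, the base-case cost-effectiveness analysis takes the NHS perspective and uses ambulance, emergency and hospital costs. No crime cost enters it, and a health index suits its inputs.

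**The case against.** The strongest reply is that this is a matter of labels. The CCA also takes a societal perspective, where victim harm belongs, so moving the item changes a row heading and leaves the societal picture unchanged. The article promises no budget impact for justice agencies. It discloses repeatedly that benefits are not monetised, and its example of an intangible is consumer pleasure or loss. On the index, the latest unit costs are to be used and inflated only where needed, and an article may leave sector-specific indices to a fuller plan.

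Part of this stands. The lack of monetised benefits is an open limitation, so the asymmetry is at most a tension in wording. The index error may be nil. But criminal justice is a perspective reported in its own right, so what goes into it determines its figure. Both rules are also stated outright, so the difficulty does not come from silence that an unseen plan might fill.

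A reader might go further and infer that the CCA double-counts call-outs, or assaults, and that sector costs in general are wrong. The article does not support that. It says "we will further deconstruct this into a CCA by reporting multisectoral costs and consequences", which describes separate reporting. A societal perspective makes a total possible but does not specify one. The valuation text in the Overview names only alcohol-related call-outs and reported crimes, although the Consequences section also associates costs with all call-outs. The content of the crime unit cost cannot be seen. A doubled ambulance cost would need a sum that is not planned, and an 8.3% index error would need an 8-year price gap that is not stated.

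**Conclusion.** Two stated rules should be changed. First, the criminal justice line contains an item that is not a police or justice-system cost under the article's own three-way split, so the figure for that perspective would overstate the sector's burden, by an amount that the article does not allow one to calculate. Second, the single health index, as written, extends to crime, retail and third-sector unit costs. Over 5 years the error is 2.5% to 10.4% for an assumed gap of 0.5 to 2 points a year, and it is zero if price years already match.

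Double counting is not shown. It is a risk only if nested or overlapping lines are later added. The health-sector line is not shown to be wrong, and the NHS-perspective cost-effectiveness analysis is unaffected.

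**What to change.** - Limit the criminal justice perspective to police and justice-system costs. Report victims' physical and emotional harm as its own row under the societal perspective, and reword the sentence on intangibles to say which intangible items are valued.
- Keep the Health Services index for health costs. Uprate crime, retail and third-sector unit costs with a general price index such as the GDP deflator, and state the price year of each source.
- As a safeguard only, state that the alcohol-related and all-call-out cost lines are nested and must not be added. If a societal total is formed, remove any victim health-care component found in the crime unit cost first.

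The cost is small: one row re-allocated, one further index and a few sentences. No new outcome data or models are needed. The victim-harm component must be separable in the published unit cost, and the planned scenarios by crime cost area already call for a breakdown of that kind. The criminal justice figure will be smaller in size, and the item removed from it will remain visible in its own row.
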